#### Secondary outcome measures

The secondary outcomes relate to the effectiveness of early integrated palliative care on (1) quality of care and healthcare services utilisation, (2) quality of life for residents and their families, and (3) quality of life at work for LTCF professionals. These expected outcomes are connected to the overall goal of palliative care, which is to improve quality of life for individuals and their families [17], and the quality perceived by relatives can influence patients’ quality of life [47]. In addition, early integrated palliative care can have a potential effect on the care pathway [48] and on the working conditions of healthcare providers [49] which could affect their quality of life [50, 51].

##### Quality of care

will be assessed in two ways: (i) by the palliative care quality indicators extracted from InterRAI-Palliative Care (InterRAI-PC) instrument [52] and (ii) by perceived quality of care as expressed by relatives of residents using the QUALI PALLI FAM questionnaire [47]. Several domains will be measured including symptom management (prevalence of negative mood, prevalence of pain that is not controlled), caregiver support (prevalence of caregiver’s distress), information and communication, coordination of care, and spiritual and emotional care support. Both tools have adequate reliability and validity [47, 52].

##### Quality of life (QoL)

for residents will be measured using the interRAI Self-Reported Quality of Life (interRAI-QOL) [53]. The InterRAI-QOL measures 10 domains: privacy, food/meal, safety/security, comfort, autonomy, respect, responsiveness of staff, staff-resident bonding, activity options, personal relationships (presence of friends). The minimum score (0) is the best outcome for quality of life, and the maximum (16–24) is the worst outcome.

##### Quality of life of informal caregivers

will be assessed using the Caregiver’s Burden Scale in End-of-Life Care (CBS-EOLC) self-questionnaire [54]. A minimum score of 16 indicates the best quality of life for informal caregivers, whereas a maximum score of 54 indicates the worst quality of life.

##### Professional quality of life at work

will be assessed using the 30-item Professional Quality of Life (ProQoL R-V) scale that measures compassion fatigue, compassion satisfaction, and burnout [55, 56]. Compassion satisfaction is defined as the pleasure derived from being able to do the work well while compassion fatigue results from giving high levels of energy and compassion over a prolonged period to those who are suffering, often without experiencing the positive outcomes of seeing patients improve [57], which seems particularly relevant in the LTCF context. The highest score suggests a good quality of life of professionals and the lowest score suggests a poor quality of life.

### Settings and participants

#### Settings

The settings of this interventional study includes 21 LTCF in three different regions of France (Ile de France, Provence-Alpes-Côte d’Azur, and Nouvelle-Aquitaine). The LTCF were recruited based on a group of seven LTCF settings per region. Purposeful sampling strategy was used for the LTCF selection. Attention was given to obtain a mix of characteristics: funding (public, private for-profit or not), geographical location (urban/non-urban territory), size (bed capacity), and affiliation or not with a hospital.

#### Participants and eligibility criteria

The study targets three categories of population: LTCF residents in need of palliative care, their family caregivers, and healthcare providers.

Recruitment of residents will be done continuously over time. All older persons aged 60 years and above who are residents in one of the participating LTCF will be potentially eligible for screening for palliative care needs. If a LTCF is too large to be included entirely, a part of the site (building, wing, floor) will be randomly selected.

For each resident identified with palliative care needs, their main informal caregiver will also be identified. Informal caregivers could be any person considered by the resident or the professional caregivers as an informal caregiver, regardless of whether this individual is a family member of the resident. With the resident’s consent, their informal caregiver will be invited to participate.

All healthcare providers and managers from the participating sites are eligible for the study, except those who will voluntarily decline to participate and those who are on a temporary work contract at the LTCF.

#### Sample size and power calculations

Proper identification of palliative care needs for a resident, the main primary outcome, served as the basis for calculation of the number of subjects required for the quantitative component of the study. Power and sample size calculations were performed using simulations written in R language based on the approach described by Baio and colleagues, and Hemming and colleagues [58, 59].

The following parameters were used in the program: number of LTCF, number of waves (i.e. groups of LTCF) from three to seven, proportion of eligible residents in need of palliative care (from 20 to 40%, size of an average LTCF is 100 residents), and proportion of identification within that sub-population (from 20 to 50%). We also considered the expected absolute minimum increase in identification of 15–30%, intra-cluster correlation (from 0.02 to 0.1), intra-individual correlation from zero (cross-sectional design) to 0.5 (cohort design) according to the open cohort design, and the fact that a resident may participate in one (cross-sectional design) to four (closed-cohort design) periods and provide as many observations. To highlight an absolute increase of 15 points to 20 points in the proportion of the residents needing palliative care and having been identified, with a 5% alpha risk, 80% power, the number of observations needed to range from 1000 to 2000. As an average LTCF may provide 25 eligible residents which may be observed two times, our 21 LTCF set has the potential for 1000 observations. Elsewhere, an increase in detection of palliative care from 50 to 65%, or from 40 to 60%, corresponds to an effect size of 0.3 or 0.4, respectively. By comparison, the Quebec trial of a multifaceted intervention on the quality of the end of life of dementia patients in long-term care showed effect sizes of 0.4 for the CAD-EOLD score measuring comfort during dying and 0.34 for peaceful death [60].

For the qualitative component, we will use a nonprobability purposive sampling to include a range of participants who could inform a deeper understanding of the phenomena investigated.

### Data collection procedures

As this study uses a convergent parallel mixed-method design [39], quantitative and qualitative data will be collected at the same time from each cluster considered a case. In accordance with the stepped wedge design, the measurements will be carried out simultaneously in all sites of the same group during the pre-intervention period (one to two measurements depending on the cluster), once at the end of the intervention period and once at the 12th month post-intervention (Fig. 2). There will be no quantitative data collected during the intervention delivery period.

Resident quantitative data will be retrieved using PICT and a subset of InterRAI-PC scales. Dedicated nurses with experience in palliative care will serve as research assistants after receiving training on the use of the above tools and the multidimensional evaluation approach. They will register data in the RAisoft database.

To collect descriptive and explanatory variables at the LTCF level, our research team developed an organizational questionnaire with two parts: (i) LTCF characteristics and functionalities: size and skill set of human resources, coordination with other community and hospital services in palliative care; and (ii) sociodemographic and medical characteristics, overall death rate of residents at the entire site.

To complement the tools used to measure outcomes, the research team developed a structured checklist of indicators to assess retrospectively and prospectively the accessibility and quality of care provided to residents with palliative care needs. Trained research assistants will retrospectively review the files of the residents for six months before the pre-implementation period and throughout the study, as well as prospectively follow-up with prospective residents with palliative care needs. Items related to consideration of residents’ needs and preferences, symptom management, resident care pathway and health service use will be checked.

Qualitative data will be collected continuously throughout the study duration. We will use a triangulation approach to data collection: individual interviews, focus groups, and participant observations, from multiple data sources.

Individual in-depth semi-structured interviews will be conducted during the pre- and post-implementation phases with professionals and managers, informal caregivers, and residents from each site, as well as with specialised palliative support teams affiliated with the participating LTCF. In addition, focus group discussions with various healthcare professionals involved in the direct care of residents (nurses, nurse assistants, psychologists, physiotherapists, occupational therapists) from nine purposively selected cases will be conducted. Interview guides specific to each group of participants will serve as data collection tools. Four themes will be explored throughout the interviews and focus groups: current practices, palliative care perceptions, quality of life at work, and barriers and facilitators of the implementation of early integrated palliative care. A researcher trained in qualitative research will conduct the individual interviews and focus groups.

Participant observations will be carried out throughout different periods of study. An observation guide was developed to collect information during the observation of care situations in LTCF. Information will be collected on several items at each LTCF, including usual palliative care practices, level of quality of routine service, processes, structural characteristics, organizational culture and professional interactions, and external factors such as the exiting of support teams in palliative care services provision and the territorial provision/organisation of palliative care. Extensive field notes will be taken, and a weekly research team meeting will be held to continuously analyse the collected observations.

### Analysis

#### Quantitative analysis

The quantitative data will be analysed using R. Statistical analysis and will be performed after a blind review of data quality issues and a database “freeze.” Due to the sequence of interventions, the analysis cannot be carried out in a blinded fashion.

A patient flow chart will be set up according to the CONSORT extension recommendations for stepped wedge design [61]. Main analysis will be performed on all included residents following the intent-to-treat principle and according to the role assigned to each period (usual care in the pre-intervention period versus experimental care in the post-intervention period) regardless of whether palliative care was implemented.

#### Descriptive analysis

The descriptive analysis will summarize baseline clinical characteristics of the study cohort. Descriptive statistics will be reported as means and medians, standard deviations, and interquartile ranges. The nominal data will be reported as percentages with two-sided 95% confidence intervals. The proportions of missing data will be calculated. Participant characteristics (eligibility criteria, demographics data at inclusion) will be described and compared by setting and reported without comparison by period.

#### Primary outcome analysis

The data analysis will be based on the comparison of data collected during pre-intervention versus post-intervention periods. The three primary criteria will be tested according to a hierarchical procedure: identification sensitivity, access, and optimal timing from a fixed sequence procedure; constructed using a pre-specified sequence of hypotheses; and endpoints ordered according to their importance [62]. All tests will be performed at the 0.05 level following the pre-specified order. Once one hypothesis is tested and the results indicate it is not significant, all subsequent tests will not be performed.

The statistical model will take into account the non-independence of the observations, as multiple evaluations may concern the same resident across time due to the use of open cohorts and several residents are included from the same LTCF. This hierarchy (three levels) leads to the use of generalized linear mixed models (GLMM) for repeated measures [63]. For dichotomous outcomes (i.e. the patient has been identified or not), we will use a Bernoulli distribution with a logistic link function, and for continuous outcomes a normal distribution with identity link function. The independent variables will be: the LTCF and the resident considered as random factors, the calendar time interval (common to all groups) considered as a fixed factor, and treatment mode for the cluster in the time interval (pre-intervention = control, post-intervention = experimental) considered as a fixed factor associated with the effect of the intervention. The chronological sequence of stepped wedge randomized trials means that the number of clusters exposed to the intervention being tested increases as the trial progresses [41].

The observation of an intervention effect may reflect the existence of an underlying secular trend that is independent of the intervention. Therefore, modelling the background secular trend is necessary to remove bias in estimating the effect attributed solely to the intervention. However, the saturated time parameterization (by J-1 indicators if there are J periods) may not be the most efficient approach if there are a large number of periods relative to the number of waves and clusters due to the reduced degree of freedom available for estimating the intervention effect. Thus, we will use a parsimonious specification with a minimum number of parameters, such as a polynomial specification to a fixed degree [64].

To test the consistency of the hypothesis of a constant effect or conversely a time-varying intervention effect, we will develop a similar model with a random effects covariate representing the interaction of time by cluster. Finally, there may be variation across clusters in the magnitude of intervention effects that will be modelled by a cluster-period-specific random effect deviation [65] as this type of modelling also takes into account the incomplete structure of the stepped wedge design.

As additional exploratory analysis, the individual and institutional characteristics as well as the intensity of intervention will be used as explanatory or confounder factors as recommended in the literature and by expert opinion. In order to minimize the dimensionality of these factors, principal component analysis or a Lasso-type technique could be applied. The possible nonlinear effects of the continuous variables will be managed through fractional polynomials. The models’ performance will be assessed by the Akaike information criterion [66], and the stability of the estimates will be checked by resampling.

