**Fig. 1 Fig1:**
[figure not shown]
Flowchart representing the research design with a convergent parallel mixed-method

As depicted below in Fig. 2, over the course of the study timeline each of the 21 participating centres will be defined as a cluster and randomly allocated to one of the seven groups. This allocation will follow a sequence similar to the observational and interventional periods. Randomisation of LTCF will be stratified by region; each group includes LTCF from the three participating regions.

The strategy used addresses issues related to incomplete design by minimizing the collection load to preserve good power by removing uninformative combinations of clusters and periods without too much alteration of the power [44]. A sequence includes: one or two pre-intervention observational periods of two months; one delivery intervention period of three months followed by an interventional consolidation period of three months; then a short-term observational period of two months; and 12 months after intervention a final observational period of two months, called autonomy.

The individual data collection is based on an open cohort: as the study progresses, some residents will leave the LTCF or die (on average 25% each year, but likely higher for subjects requiring palliative care), while others will be admitted to the LTCF or begin to require palliative care and will be included at a later date.

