### Outcome evaluation

#### Primary outcome measures

The primary outcome measures relate to the accurate identification of palliative care needs and early access to palliative care for residents in LTCF context. These will be assessed through a comparison of the pre- and post-intervention periods, with the main comparison focusing on the latest evaluation (autonomy). The following will be measured and compared:

1) Identification sensitivity: This main criterion is the proportion of residents identified by the LTCF team as in need of palliative care among those with “potential” palliative care needs identified proactively by a dedicated research nurse using “Gold Standards Framework Proactive Identification Guidance” [45] and the Palliative Care Indicator Tool (PICT) [46].

2) Access: The proportion of residents with effective access to palliative care delivery among those identified as in need of palliative care (with or without referral to the specialist palliative care service).

3) Optimal timing: We postulate that during the pre-intervention phase, the identification of residents’ palliative care needs is delayed and may not be systematically followed by the delivery of palliative care. Therefore, we will estimate the time gain by focusing on the interval between the time residents are identified as in need of palliative care and the time of their death (or discharge, withdraw from follow-up). An increase in this time can be interpreted as a shortening of the identification delay but also as an extension of the delivery period of palliative care and the identification of the need for palliative care, both of which would support the effectiveness of palliative care.

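### Criterion 3 (optimal timing) is a censored time to death but falls to a normal, identity-link model; the bias can reach months, in a direction set by a closing date the article does not state

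*Protocol article*

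**What the plan says.** Primary outcome measures, item 3, defines the criterion as a duration that starts when the need is identified and ends at "the time of their death (or discharge, withdraw from follow-up". A longer interval is read as evidence of benefit. The same section makes the autonomy window the main comparison.

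Primary outcome analysis places this criterion in the confirmatory sequence: "The three primary criteria will be tested according to a hierarchical procedure: identification sensitivity, access, and optimal timing". It adds: "All tests will be performed at the 0.05 level following the pre-specified order". The model is a generalised linear mixed model in two forms: Bernoulli with logistic link for dichotomous outcomes and, "for continuous outcomes a normal distribution with identity link function". LTCF and resident are random factors. Time enters as "the calendar time interval (common to all groups) considered as a fixed factor", later reduced to a parsimonious form such as a polynomial. There is one treatment term, pre-intervention against post-intervention.

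The schedule, in the Process evaluation design section, has one or two control windows of two months, three months of delivery, three of consolidation and a two-month short-term window. It ends with "12 months after intervention a final observational period of two months, called autonomy".

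The only survival model is under Secondary outcome analysis. It is a Cox model for residents' survival time, with a time axis based on admission.

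**The concern.** Criteria 1 and 2 are proportions, so criterion 3 falls to the normal model by elimination. The article never assigns it by name, but it gives no other primary model.

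That model does not fit this outcome in two ways. It has no censoring: a resident still alive when observation stops has no interval, or a truncated one entered as if complete. It also gives discharge and withdrawal the same standing as death, so fewer discharges would count as earlier identification.

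The time available for observation also depends on the window in which the resident was identified, and window is tied to treatment status. The treatment coefficient therefore mixes a change in timing with a difference in follow-up. The third confirmatory test could then report a gain or a loss that the schedule alone produces.

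**Working it through.** The article gives no expected time, standard deviation, event count or power for criterion 3, so there is no stated figure to reproduce.

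**Follow-up by window.** Set month 0 at the start of the last control window. Control runs over months 0-2, delivery and consolidation 2-8, short-term 8-10. Autonomy runs over 20-22 if the 12 months start at the end of consolidation. Assume that follow-up closes with the site's own autonomy window, at month 22:
- identified in the last control window: 22 − 2 = 20 to 22 − 0 = 22 months (22 to 24 for an earlier, adjacent control window)
- identified in the short-term window: 22 − 10 = 12 to 22 − 8 = 14 months
- newly identified at autonomy: 0 to 2 months

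**Mean observed interval, no true effect.** Assume exponential time to death T with mean μ, and remaining follow-up C uniform on (a, b). Then E[min(T, C)] = μ − μ²/(b − a) × (e^(−a/μ) − e^(−b/μ)). For a 6-month median, μ = 6/ln 2 = 8.656 and μ²/2 = 37.46:
- earlier control (22, 24): 8.656 − 37.46 × (0.0788 − 0.0625) = 8.05
- last control (20, 22): 8.656 − 37.46 × (0.0992 − 0.0788) = 7.89
- short-term (12, 14): 8.656 − 37.46 × (0.2500 − 0.1984) = 6.72
- autonomy (0, 2): 8.656 − 37.46 × (1 − 0.7937) = 0.93

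These means differ only because follow-up differs.

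**Single pre/post term, site-specific closing.** With one control window per site, LTCF effects and a linear time trend, each site has three means and three parameters, so the fit is exact. The slope comes from the two post-intervention windows: (0.93 − 6.72)/12 = −0.4825 per month. Carried over the 8 months from control to short-term, it predicts 7.89 − 8 × 0.4825 = 4.03. The treatment term takes the rest: 6.72 − 4.03 = **+2.69 months**, a false gain. For a 4-week median the means are 1.33, 1.33 and 0.64, and the same steps give 8 × 0.69/12 = **+0.46**.

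**Separate autonomy term, site-specific closing.** The slope now comes from sites with two control windows: (7.89 − 8.05)/2, or −0.079 unrounded. Over 20 months this predicts about 7.89 − 1.58 = 6.31 at autonomy. The term is 0.93 − 6.31 = **−5.38 months**, a false loss.

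**Simulation** (7 groups of 3 LTCF, 2-month stagger, quadratic time, no true effect):

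| Usual-care interval | Separate autonomy term, site closing (months) | Single term, site closing, mixed model: mean (share of runs falsely favouring the intervention) |
|---|---|---|
| median 7 days | −0.05 | +0.02 (8%) |
| median 4 weeks | −0.71 | +0.29 (42%) |
| median 6 months | −5.5 | +1.98 (70%) |
| 50% exits per year | −5.8 | +1.26 (30%) |
| 25% exits per year | −4.4 | +0.74 (5%) |

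The last column uses 12 residents per LTCF-window and 60 runs per scenario. By least squares the single-term bias ran from +0.04 to +2.9 months. With a common closing date, the single term and quadratic time, it was −0.24 to +0.34. That last result depends on the polynomial: with a linear trend and a 3-month stagger it was +1.17 at the 6-month median.

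**Check of the remedy.** A right-censored Cox model from identification, autonomy against control, gave hazard ratios of 0.95 to 1.03 with no effect for medians of 7 days to 12 months. It gave 0.45 to 0.51 when the true interval was doubled. At 25% exits per year the no-effect ratio was 0.84, with about 98% of autonomy times censored.

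**The case against.** The strongest objection is that the article does not fix what the bias depends on. It gives no closing date. Data collection procedures describes file review and prospective follow-up over the whole study, which fits a common closing date at least as well as site-by-site closing. Under a common date, with the stated single term and a quadratic trend, the null bias nearly vanishes and a doubled interval shows a gain (+0.30 to +4.6 months). The open cohort also lets residents identified earlier be present at autonomy, which lessens the imbalance. All of this stands, and it limits what can be said about direction.

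A reader comparing raw window means might infer that autonomy always shows a large loss, even if the true interval doubles (7.89 against 0.96 months at a 6-month median). The documents do not support that. It needs site-specific closing, only newly identified residents, and a raw contrast or separate autonomy term. It also needs a usual-care median above about 13 days. The Background section cites a median of seven days in geriatric centres (for specialised services, so only a proxy). At that value the null loss is 0.05 month and doubling shows a gain of 0.12.

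It can also be said that the parenthesis in item 3 lists censoring ends, and that details belong in an analysis plan. But a normal identity-link model cannot honour censoring, and the article commits to that model. The secondary Cox model has another outcome and another origin. That criterion 3 comes third in the sequence limits how often it is tested, not whether the test is valid.

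With one value per resident, the resident random effect merges with the residual. This is untidy but does not bias the treatment estimate.

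**Conclusion.** The point holds in this form: the only primary model available to criterion 3 ignores censoring and treats discharge and withdrawal as death. Its estimate can be off by months with no true effect. Size and direction depend on the closing date and on whether autonomy has its own term, and the article settles neither. At a 6-month median with site-specific closing, the bias is about +2.7 months with the single term and about −5.4 with a separate autonomy term. It is little with a common closing date, the single term and quadratic time.

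The assumptions are exponential times, uniform identification within windows, a 2-month stagger, 12 months counted from the end of consolidation, and no carry-over of earlier-identified residents. The bias is negligible if usual-care intervals are about a week and large if they are months.

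A reader might also infer that criterion 3 cannot be evaluated at autonomy. That goes too far: a censored analysis recovers the effect there, though imprecisely when almost all times are censored.

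**What to change.** Replace the normal model for criterion 3 with a right-censored time-to-event analysis:
- one record per resident, clock starting at identification, phase assigned by date of identification
- death as the event; discharge and withdrawal as censoring or competing events, stated in advance
- residents alive censored at a stated closing date
- LTCF clustering and calendar time in the model

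If a restricted mean is used, choose a horizon that every resident in the compared windows can reach. For control against short-term this is about 12 months if follow-up closes with the site's autonomy window and the 12 months run from the end of consolidation.

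Keep autonomy as the main comparison. State that its estimate covers only the short follow-up available there and will be imprecise unless deaths are recorded beyond that window.

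The cost is some extra analysis work and a less precise autonomy estimate.

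### The main comparison is set at the autonomy evaluation, but the primary model has one pooled pre/post term, so the tested coefficient is the autonomy effect only if the short-term and autonomy effects are equal

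*Protocol article*

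**What the plan says.** Under Primary outcome measures, the article compares pre- and post-intervention periods "with the main comparison focusing on the latest evaluation (autonomy").

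The Process evaluation design section gives each LTCF "one or two pre-intervention observational periods of two months", three months of delivery and three of consolidation, "then a short-term observational period of two months", and "12 months after intervention a final observational period of two months, called autonomy". Data collection procedures confirms two post-intervention measurements per site.

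The analysis sections do not separate these two windows:
- Quantitative analysis assigns roles as "usual care in the pre-intervention period versus experimental care in the post-intervention period".
- Primary outcome analysis opens with "The data analysis will be based on the comparison of data collected during pre-intervention versus post-intervention periods" and specifies "treatment mode for the cluster in the time interval (pre-intervention = control, post-intervention = experimental) considered as a fixed factor", alongside random LTCF and resident effects and a low-degree polynomial in calendar time.
- For a time-varying effect, the same section says "we will develop a similar model with a random effects covariate representing the interaction of time by cluster".

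The three primary criteria are tested in fixed order at 0.05, and testing stops at the first non-significant result. Sample size and power calculations states 1000 to 2000 observations for 80% power to detect 15 to 20 points.

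**The concern.** The article names one comparison as main and specifies a model with no parameter for it. The autonomy window exists to show whether practice holds once support has ended, so equal effects in the two windows are the question and cannot simply be assumed.

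If the effects differ, the reported estimate can mislead in either direction. A short-lived gain may be read as sustained, and a gain that builds over the year may be missed. Because this coefficient also gates the sequence, it decides whether access and timing are tested at all.

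**Working it through.** **1. The plan's own figures.** With Cohen's h = 2·asin(√p2) − 2·asin(√p1), 50% to 65% gives 0.305 and 40% to 60% gives 0.403, matching the stated 0.3 and 0.4. The available observations are 21 × 25 × 2 = 1050, stated as 1000. The 1000 to 2000 range comes from simulations that are not shown and cannot be reproduced exactly. A pooled model with a constant effect of 15 points, 2-month steps, quadratic time, ICC 0.02 to 0.1 and cluster autocorrelation 0.8 to 1 needs 1008 to 1728 observations. The stated range is thus compatible with a pooled effect.

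**2. Concurrent controls.** Fig. 2 is not shown, so the step length s between groups is assumed to be 2, 3 or 4 months. Group g crosses over at (g − 1)s, and group 7's last control window closes at 6s. A post-intervention window opening L months after crossover can overlap a control window only if (7 − g)s > L. The short-term window has L = 3 + 3 = 6. For autonomy, L = 3 + 3 + 12 = 18 if the 12 months run from the end of consolidation, or 3 + 12 = 15 if they run from the end of delivery.

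| Groups with concurrent controls | s = 2 | s = 3 | s = 4 |
|---|---|---|---|
| Short-term, L = 6 | 3 of 7 | 4 of 7 | 5 of 7 |
| Autonomy, L = 15 | 0 of 7 | 1 of 7 | 3 of 7 |
| Autonomy, L = 18 | 0 of 7 | 0 of 7 | 2 of 7 |

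**3. What the single coefficient estimates.** Generalised least squares was applied to LTCF-window means (a linear approximation, 25 residents per window), with fixed calendar time and random site effects. The expected pooled estimate is wS·δS + wA·δA, with wS + wA = 1, where δS and δA are the short-term and autonomy effects. Over s = 2 to 4, L = 15 or 18, ICC 0.02 to 0.1 and autocorrelation 0.5 to 1, wA runs from about −0.8 to +0.2 and is negative in most layouts.

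One layout as an example: s = 2, L = 18, ICC 0.05, autocorrelation 1, individual correlation 0.3, quadratic time, one pre window in the first four groups and two in the rest. Here wS = 1.56 and wA = −0.56.
- Short +15, autonomy +15: 1.56 × 15 − 0.56 × 15 = +15.0 points.
- Short +15, autonomy 0: 1.56 × 15 = +23.4.
- Short +15, autonomy +30: 23.4 − 16.8 = +6.6.
- Short +5, autonomy +20: 7.8 − 11.2 = −3.4.

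Over the whole weight range, short +15 with autonomy 0 gives 15 × (1 − wA), that is +12 to +27 points.

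A simulated logistic mixed model (s = 2, 150 runs per scenario, no resident effect, mean estimates only) moves the same way. True log odds ratios of 0.62 then 0 gave a pooled mean of 0.90; 0.62 then 1.39 gave 0.28; 0 then 0.62 gave −0.30. The direction is the same at 3- and 4-month steps.

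**4. The planned check.** A random time-by-cluster effect describes mean-zero departures of sites from the common trend. A shift in the mean effect from the short-term to the autonomy window is a fixed contrast in time since intervention, and no term estimates it. The cluster-period deviation that the article also plans addresses heterogeneity between sites and does not supply that contrast either.

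**5. Precision of a separate autonomy term.** In the example layout with 25 residents per window (72 LTCF-windows, 1800 observations), power for 15 points at autonomy is 18%, 33% and 50% at 2-, 3- and 4-month steps. The pooled term under a constant effect has 96% to 99%. Over the range in step 3, the autonomy difference detectable at 80% power is about 13 to 55 points.

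**The case against.** A journal article condenses the protocol, and the coding of two post-intervention windows could sit in the unseen full document. That lowers confidence about what will finally be run. It does not remove the conflict, because the article itself fixes the main comparison, the treatment coding and the constancy check, and they do not agree.

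The numerical objections carry more weight. The size and sign of wA depend on a calendar that is not visible, on the time model and on the correlation between periods. With cluster autocorrelation 0, wA is negative in only about half of the layouts (45% to 50%). If the two effects are equal, the pooled coefficient is unbiased and more precise. All of this stands, so the figures are illustrations.

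A reader might infer three stronger things that the documents do not support:
- **That the autonomy effect always counts negatively.** It does so in most layouts, but the range reaches about +0.2.
- **That concurrent controls exist only if steps exceed 3 months.** This needs the 12 months to run from the end of consolidation. Counted from the end of delivery, one group has them at 3-month steps.
- **That the tests should therefore move to the short-term effect.** The article chose autonomy as main, and better concurrent control of the short-term window does not by itself overturn that choice.

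**Conclusion.** The inconsistency is in the text and needs no assumption: the comparison called main and the coefficient that is tested are the same quantity only if the short-term and autonomy effects are equal. The planned check does not estimate a mean difference between them. Followed as written, the plan can give a wrong answer to its main question.

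The size rests on the assumed calendars and correlations: an autonomy weight of about −0.8 to +0.2, mostly negative, and a detectable autonomy difference of about 13 to 55 points. A reader might conclude that the trial is underpowered for autonomy. A shortfall is likely in many layouts, but the lower end of the range lies below the 15 to 20 points targeted, so it is not established. What can be said is that the article does not show that its power statement refers to the autonomy contrast.

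**What to change.** 1. In Primary outcome analysis, replace the single treatment indicator by two, short-term and autonomy, each against usual care and adjusted for calendar time. Align the description of period roles in Quantitative analysis.
2. Report both coefficients, and use the test that they are equal as the check for a time-varying effect in place of relying on the random time-by-cluster term.
3. State which coefficient gates the fixed sequence and make it agree with Primary outcome measures. That is the autonomy coefficient, unless the sponsor rewrites that section.
4. In Sample size and power calculations, restate the power or detectable difference for that contrast, using the actual Fig. 2 calendar.

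The cost is revised wording, one extra model term and a rerun of the power simulation; no new data are needed. The downside is a wider interval for the autonomy effect and its open reliance on the modelled calendar trend, which should be stated with the result.
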